## Abstract

**Background:**

Across Ohio, parental substance abuse has contributed to a marked increase in the number of children in foster care. Children exposed to parental substance use have a higher likelihood of physical abuse and neglect, and consequently a variety of physical, psychological and cognitive problems. The Enhancing Permanency in Children and Families (EPIC) program is a collaborative effort between the Ohio State University College of Social Work, two county offices of the Ohio Department of Job and Family Services, two juvenile courts and local behavioral health agencies. The goal of EPIC is to use three evidence-based and evidence-informed practices to reduce abusive and neglectful parenting, reduce addiction severity in parents, and improve permanency outcomes for families involved with the child welfare system due to substance abuse.

**Methods:**

EPIC is a quasi-experimental study. Under the program**,** child welfare-involved adults who screen positive for substances are matched with a peer recovery supporter. Participants are also incentivized to participate in family treatment drug court, medications for opioid use disorders and home-based parenting supports. Participating adults (*N* = 250) are matched with comparison groups from counties participating in a separate intervention (Ohio START) and to those receiving treatment as usual, resulting in a final sample of 750 adults. Primary outcomes including addiction severity, child trauma symptoms, resilience, and attachment are assessed at baseline and at program completion. Additional outcomes include timely access to treatment services, length of placement in out-of-home care and recidivism into the child welfare system.

**Discussion:**

This intervention formalizes cross-system collaboration between child welfare, behavioral health and juvenile courts to support families affected by addiction. The use of three evidence-based or evidence-informed strategies presents the opportunity to determine specific strategies that are most effective for reducing addiction severity. Lastly, the intervention combines several sources of funding to bolster sustainability beyond the life of the Regional Partnership Grant (RPG).

**Trial registration:**

NCT04700696. Registered January 7, 2021-retrospectively registered.

**Supplementary Information:**

The online version contains supplementary material available at 10.1186/s12889-021-10668-1.

## Introduction

## Background

A significant proportion of children in the United States are exposed to substance-using parents, with prior estimates suggesting 12% of children live in a household where at least one parent is abusing or dependent on alcohol or other drugs [1]. Children exposed to parental substance misuse experience higher risks for any array of physical, cognitive, psychological, and social harms [2]. Some of these adverse consequences are likely due to parental drug abuse or dependence being associated with a higher likelihood of child physical abuse or neglect, particularly when the perpetrator is a biological parent [3, 4].

While no conclusive national estimate of the number of children entering the child welfare system due to parental substance use exists, an estimated 1 in 5 children live in a home with an adult who misuses drugs and alcohol [5]. Caseworkers estimate that 50–80% of parents on their caseloads have problems with substance use and that their children are more likely to enter foster care [6–8]. The Fourth National Incidence Study of Child Abuse and Neglect found that drug use was a factor in 9.5% of cases of abuse and 12.5% of all neglect cases [4]. Parents with a diagnosed substance use disorder are more likely to be physically abusive, commit child neglect, and have a higher child abuse potential than those without a diagnosed substance use disorder [9, 10]. In fact, children in these families are two times more likely to be at risk for child maltreatment [11].

This evidence is especially relevant in Ohio, which has the highest rates heroin and synthetic opioid-related deaths in the country [12]. Between 2016 and 2017, Ohio saw an 18.4% increase in the rate of drug overdoses due to prescription opioid misuse. In 2017, there were 46. 3 opioid-related deaths per 100,000 people, more than double the national rate of 13. 3 deaths per 100,000 [12]. While the national rate of heroin overdose decreased between 2016 and 2017, at 9. 2 deaths per 100,000 persons, the rate of heroin deaths in Ohio remains significantly higher than the national rate of 5 deaths for every 100,000 Americans [12].

These trends have overwhelmed Ohio’s child welfare system. Fifty percent of children placed in state custody were due to parental substance use, with nearly half (28%) due to opioid use [13]. Consequently, the number of children placed in custody increased by 11% [13].

### Need for services

Fairfield and Pickaway are adjacent counties in central Ohio. As of the 2010 census, Fairfield County had a population of 146,156, largely composed of Whites (90. 2%), with Blacks representing 6.0% of the population. Southwest of Fairfield is Pickaway County, with a much smaller population of 55,698. Whites make up 94.5% of the population followed by Blacks at 3.4%. Both counties have high rates of opioid-addicted families involved with the child welfare system. The rate of investigations for child maltreatment in Fairfield County is above the state average at 48.09 per 1000 children [14]. Though the rate of child maltreatment investigations is lower in Pickaway County (14.29 per 1000), the number of children in out-of-home care rose over 200% from 23 in 2013 to 73 in 2018 [14, 15]. According to a survey conducted by the Public Children Services Association of Ohio (PCSAO), 79% of families involved in Fairfield County Children’s Services and 67% of families in Pickaway County Children Services have identified substance use problems, both higher than the state-wide average of 50% [16]. In Pickaway County, all the substance-involved families were due to opioid (including heroin) misuse, while 58% of all cases in Fairfield County involved opioids [16]. These rates are over twice the state average of 28% [16]. Thus, while opioid addiction is a particular concern, all types of substance use are affecting children involved in the child welfare system.

The two county agencies have seen a significant increase in the number of children on their caseloads. This increase is attributed to the increase in parental substance abuse and has contributed to a higher number of children in foster care and rising foster care costs. In 2013, Pickaway County Children Services placed 10 children in foster care in contrast, a total of 46 children were placed in foster care in 2018 [16]. In Fairfield County, the overall number of children in agency custody has remained steady from previous years, yet the costs to house these children has increased dramatically due to the needs of the children. In 2014, the agency spent $1.6 million on out-of-home placement costs, by 2018, the cost to house the same average number of children jumped to nearly $ 3.1 million [14]. Many of these children are placed with relatives who may be ill-equipped to address the specific needs of children exposed to substance use problems. As there are limited non-relative foster homes available, children are often placed several hours away from the agency creating challenges for staff to meet face-to-face requirements and provide regular visitation between parents and children.

### Rationale for study

Both counties have taken significant steps to address the needs of families, including the implementation of Ohio START (Sobriety, Treatment, and Reducing Trauma) [17].

Fairfield and Pickaway counties also have Family Treatment Drug Courts (FTDC) in operation. FTDC includes frequent court hearings, judicial monitoring, substance abuse treatment, drug testing, and rewards and sanctions linked to parental compliance with service plans [18]. However, only six residential or intensive outpatient substance use providers are located within the boundaries of the two counties, with only one providing residential or detoxification facilities. While a 31bed facility recently opened in Pickaway county [19], the demand for detoxification beds still outweighs the current supply. Fairfield County has little infrastructure to support the use of medications for opioid use disorders (MOUD) and has not used it systematically for child welfare families. Further, while service providers and local governments tend to think in terms of county lines, families do not use that same thought process when seeking help. In this way, the patchwork structure of alcohol and other drug (AOD) services inhibits the ability of both counties to address the AOD needs of families involved in the child welfare system.

Funded by the federal Regional Partnership Grant (RPG) Program, the Enhancing Permanency in Children and Families (EPIC) is a partnership between child welfare, juvenile count court  and behavioral health, to holistically address substance misuse and associated parenting needs of child welfare-involved families.

## Methods / design

The overall goals and objectives of the intervention are:
Increase timely access to services among substances abusing parents involved in the child welfare system in Fairfield and Pickaway counties1.1 Develop procedures to coordinate services between the child welfare system, substance abuse and behavioral health providers, and juvenile/family court in a specified single MOU.1. 2 Conduct substance abuse and trauma-exposure screening and assessment within 30 days of entering the child welfare system.1. 3 Reduce the wait time between referral to services and initiation of substance use and behavioral health services.Enhance child safety and improve permanency2.1 Reduce length of stay in out-of-home placement for children in EPIC program compared to substance-affected families not receiving EPIC.2. 2 Increase rates of reunification among families involved in EPIC compared to substance-affected families not receiving EPIC.2. 3 Reduce recidivism for child welfare investigations and re-entries into foster care among parents receiving EPIC compared to substance-affected families not receiving EPIC.2.4 Identify which intervention components implemented via EPIC were more likely to increase positive outcomes for families.Increase child, parent, and caregiver well-being3.1 Decrease substance use/abuse addiction severity among parents and the percentage of parents completing substance abuse treatment who maintained abstinence post-treatment.3. 2 Reduce trauma symptoms experienced by children.3. 3 Increase resilience and attachment in children.3.4 Increase knowledge about trauma-exposure among kinship caregivers.3.5 Improve parenting among kinship caregivers.

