### Evaluation design

To evaluate EPIC, a quasi-experimental design will be employed through a two-stage sampling procedure. This design provides the ability to assess (1) the effects of EPIC on access to services for the families in the two intervention counties, and (2) the independent effects of additional services provided under EPIC that may be over and above interventions provided by Ohio START and treatment as usual (TAU). In the first stage, two comparison counties will be identified for each of the two intervention counties. One comparison county will be part of the Ohio START program while the second will be a county that has no major interventions to address substance use among child welfare families. Counties are matched based on child population size, rate of child protective services referrals, percent of naloxone administrations per adult population, percent white, percent poverty, child welfare tax levy, and to the extent possible, behavioral health service availability. During the second stage, EPIC families (*N* = 250) are matched with substance using families in Ohio START (*N =* 250) and those receiving treatment as usual (*N =* 250).

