#### Power analysis

We performed a series of power analyses using G*Power [44] and for each analytic method. Assuming a small effect size of 0. 2, we will be able to reject the null hypothesis with probability (power) of 1.00 (survival analysis, *N* = 750), 0.81 (logistic regression, *N* = 750), 0.88 (paird t-tests; *N* = 250) and 0.99 (linear regression, *N* = 250). The Type I error probability associated with these tests is 0.05. A detailed report is presented in Additional file 1.

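### Objectives 2.1 to 2.3 compare EPIC with one undivided group of non-EPIC families, while the evaluation design claims effects beyond Ohio START and beyond usual care separately; the two contrasts need to be named and powered.

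*Protocol article*

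**What the plan says.** In the protocol article, the objectives listed under Methods / design share one comparator.

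- Objective 2.1: "Reduce length of stay in out-of-home placement for children in EPIC program compared to substance-affected families not receiving EPIC".
- Objective 2.2: "Increase rates of reunification among families involved in EPIC compared to substance-affected families not receiving EPIC".
- Objective 2.3, on recidivism: "among parents receiving EPIC compared to substance-affected families not receiving EPIC".

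The Evaluation design section is more specific. Its second aim is to assess "the independent effects of additional services provided under EPIC that may be over and above interventions provided by Ohio START and treatment as usual". EPIC families (250) are to be "matched with substance using families in Ohio START (*N =* 250) and those receiving treatment as usual (*N =* 250").

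The Statistical plan assigns survival analysis to length of stay and logistic regression to reunification and later investigations. It refers to program effects and activities, and states no contrast between groups. The Power analysis assumes an effect size of 0.2 and a type I error of 0.05. It gives 1.00 for survival analysis and "0.81 (logistic regression, *N* = 750") for logistic regression; both figures use all three groups. Details are left to Additional file 1, which is not shown.

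**The concern.** Whether EPIC does better than non-EPIC families taken together, and whether EPIC adds something to Ohio START, are different questions with different null hypotheses. The objectives as worded ask the first. The second aim of the evaluation design needs the second, and a separate comparison with TAU as well.

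The difference matters because Ohio START is an active program, which the Rationale for study says both EPIC counties already implement. The TAU counties are chosen for having no major intervention. If START helps families, a comparator that mixes START with TAU sits below START. EPIC can then beat the mixture without adding anything to START, and a reader holding the article could take that result as evidence for the second aim. The only power quoted for these outcomes, at N = 750, does not describe a 250 v 250 comparison either.

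**Working it through.** **Inputs from the article.** Three groups of 250, total 750; effect size 0.2, metric not given; alpha 0.05, sidedness not given. The article gives no expected reunification rates, so those below are assumptions.

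**1. The plan's own power figures.** For a standardized difference d, power = Φ(d·√(n₁n₂/(n₁+n₂)) − z), with z = 1.96 two-sided or 1.645 one-sided.

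The paired t-test figure (0.88, N = 250, d = 0.2) reproduces: the two-sided noncentral t gives 0.883.

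The logistic 0.81 cannot be reproduced uniquely:

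| Reading (N = 750, effect 0.2) | Two-sided | One-sided |
|---|---|---|
| 250 v 500 | 0.733 | 0.826 |
| 375 v 375 | 0.782 | 0.863 |
| Continuous predictor, log OR 0.2, assumed base rate 0.3 | 0.709 | 0.807 |

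The survival figure of 1.00 is not reached with log HR 0.2 even if all 750 have events (0.73 with 1:2 allocation, 0.78 with 1:1), nor with HR 0.8 (0.82 and 0.86). It is reached with, for example, HR 1.5. The power figures therefore do not show which contrast was meant.

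**2. What the objectives would test if taken literally.** Write E, S and T for the reunification proportions in EPIC, START and TAU. With S and T groups of equal size:

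E − (S + T)/2 = ½[(E − S) + (E − T)].

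If E = S, this equals ½(S − T), which is not zero when START beats TAU.

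**3. Size under assumed rates.** For T = 40% and S = E = 50%, the pooled difference is 0.50 − 0.45 = 0.05. The overall proportion is (125 + 225)/750 = 0.467. The standard error is √(0.467 × 0.533 × (1/250 + 1/500)) = 0.0386, so the expected z is 1.29 and the chance of a significant result in EPIC's favour is Φ(1.29 − 1.96) ≈ 0.25. Simulation (200,000 trials per row, 250 per group, two-sided 0.05) gives:

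| TAU | START = EPIC | Pooled test favours EPIC | EPIC v START rejects (either direction) |
|---|---|---|---|
| 40% | 50% | 0.258 | 0.055 |
| 40% | 55% | 0.499 | 0.053 |
| 40% | 60% | 0.746 | 0.050 |

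By the normal approximation, with TAU anywhere from 30% to 60%, the pooled figure is 25–27% for a 10-point gap, 49–56% for 15 points and 74–84% for 20 points. With EPIC 55%, START 60% and TAU 40%, the pooled difference is again 0.55 − 0.50 = 0.05. The test favours EPIC in about 25% of trials although EPIC is worse than START.

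**4. Power of the contrast that the second aim needs.** With 250 v 250 and d = 0.2: 0.2 × √125 = 2.236. Two-sided power is Φ(2.236 − 1.96) = 0.61; one-sided it is Φ(2.236 − 1.645) = 0.72. Two-sided power of 80% would take about 393 per group.

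**The case against.** The strongest reply is that no passage states the test criticised here. The objectives are program goals, not null hypotheses. The comparators are properly set in the Evaluation design section, and the objectives' phrase can serve as an umbrella for its two groups. A model with a three-level group term would also be fitted to all 750 families, so N = 750 is no evidence of pooling. The contrasts may be fixed in a statistical analysis plan or in Additional file 1, neither of which is shown.

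Most of this stands. A reader might infer that the trial will pool START and TAU, or rely on an overall three-group test, and so will credit EPIC with START's effect. The documents do not support that: no pooled or overall test is stated, and step 1 shows that the power figures do not identify one. Nor is it true that the pooled null fails whenever START beats TAU. With TAU 40%, START 50% and EPIC 45%, EPIC equals the average and the pooled null holds. The claimed added effect also refers to START and TAU together, as one of two aims, not to START alone. Finally, a significant pooled result would be correct for the objective as literally worded; the error would lie in reading it as an effect beyond START.

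What the reply does not remove is the mismatch in the text. The comparator in the objectives is stated, not left out, and it differs from the one that the second aim requires. An analysis plan that followed the objectives faithfully would carry the problem forward.

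**Conclusion.** The point holds as an inconsistency between the objectives and the evaluation design, not as a demonstrated error in the planned analysis. If objectives 2.1 to 2.3 are tested as worded, a benefit that START already gives can appear as an EPIC effect in roughly a quarter to three quarters of trials, for assumed START–TAU gaps of 10 to 20 percentage points. A direct EPIC v START test stays at about 5%. These rates rest on assumed reunification proportions and ignore matching and clustering by county. They were worked out for the binary outcome only; length of stay was not simulated. The power of 0.61 for 250 v 250 depends on reading the effect size of 0.2 as a standardized difference, which the article does not confirm.

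**What to change.** - In objectives 2.1 to 2.3, replace the single comparator with two named comparisons: EPIC v Ohio START and EPIC v TAU.
- In the Statistical plan, fit each survival and logistic model to all 750 families with a three-level group term, and report both contrasts.
- Base any statement that EPIC adds to Ohio START only on the EPIC v START contrast.
- In the Power analysis, give the metric and sidedness of the effect size and restate power for 250 v 250. For a standardized difference of 0.2 this is about 0.61 two-sided or 0.72 one-sided.

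The cost is in wording and one recalculation; the two comparison groups are already separate by design. The downside is a lower stated power for each claim than the figures now quoted at N = 750.

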### Study components

EPIC participants are incentivized to participate in (1) family treatment drug court (FTDC), with medications for opioid use disorders (MOUD); (2) peer recovery support and (3) home-based parenting supports based on the Nurturing Parenting Program [20].

#### FTDC with MOUD

FTDC is considered the most effective intervention to improve substance abuse treatment initiation and completion in child welfare populations [21]. Parents who participate in FTDC are more likely to enter substance use treatment, get into treatment quicker, stay in treatment longer, and complete treatment more often [22–24]. Additionally, families who complete FTDC are more likely to be reunified with their children as compared to parents who do not participate [22–25]. To bolster the effects of FTDC, EPIC participants also have access to MOUD, which has been shown to reduce withdrawal symptoms, lower the risk of relapse, address cravings, and provide medical supervision for individuals struggling with addiction [26]. Further, MOUD is associated with an increased likelihood that children will remain in their parents’ custody [27].

*Peer recovery supporters*—also called “recovery coaches”— are advocates for parents and their primary focus is to help get parents into treatment and support them so that they stay there. Peer recovery supporters are certified by the Ohio Department of Mental Health and Addiction Services [28] and must complete 40 h of in-person training, 16 h of online training, and pass a test. They are individuals who formerly had substance use issues, but have been clean and sober for at least 3 years. Peer recovery supporters provide comprehensive clinical assessments, service planning, referral, advocacy, case management, and outreach services. Peer recovery supporters have had great success in reducing substance use and improving child welfare outcomes. Peer recovery supporters improve access to substance use treatment, decrease time children spend in out-of-home care, increase the odds of reunification, decrease maltreatment recidivism, and reduce racial disparities in reunification [29–31]. Under EPIC, peer recovery supporters are trained and supervised by two partner behavioral health agencies, Ohio Guidestone and Integrated Services. Peer recovery supporters make individual or joint home visits with child welfare caseworkers and are otherwise available via phone and text as needed. They also attend multi-disciplinary child welfare team meetings to provide expert consultation on cases.

The third and final component of EPIC is *parenting support (Relational Skill Building)* based on the Nurturing Parenting Program (NPP) [20]. NPP focuses on parental expectations of children, empathy toward children’s needs, alternatives to corporal punishment, appropriate parent-child roles, and children’s power and independence [32]. Under EPIC, the program is further enhanced with modules specific to substance use. For example, unexpected challenges related to administering naloxone, a drug that is used to revive individuals who have overdosed on opioids and for kinship caregivers, ways to maintain safe relationships with biological parents. Under EPIC, parents and kinship caregivers may participate in the home-based relational skill building intervention.

